## Abstract

**Background:**

Promoting of local healthcare planning is crucial for assisting public health nurses in improving community health inequities. However, there is no effective educational program for developing relevant skills and knowledge among these nurses. Therefore, this study aims to assess the feasibility of a newly developed web-based self-learning program to promote the involvement of public health nurses in the local healthcare planning process.

**Methods:**

A pilot randomized control trial randomly allocated eligible public health nurses to intervention and control wait-list groups [1:1]. The former will be exposed to six web-based learning modules from July to October 2021. After collecting post-test data, the wait-list group will be exposed to the same modules to ensure learning equity. The primary outcome will be evaluated by implementing a validated and standardized scale designed to measure public health policy competencies at the baseline and post-intervention, while secondary outcome will be measured on an action scale to demonstrate the necessity of healthcare activities. The third outcome will be the knowledge and skills related to local healthcare planning by public health nurses. The participants will provide feedback through free descriptions on the trial feasibility and a web-based self-learning program to identify improvement points for continual refinement.

**Discussion:**

The results will provide suggestions in preparation for a future definitive randomized controlled trial. This will provide preliminary data for an intervention aimed at improving relevant competencies among public health nurses who are tasked with resolving health inequities in their respective communities through local health planning.

**Trial registration:**

The protocol for this study was registered with the University Hospital Medical Information Network Clinical Trials Registry and approved by the International Committee of Medical Journal Editors (No. UMIN000043628, March 23, 2021).

**Supplementary Information:**

The online version contains supplementary material available at 10.1186/s40814-022-01054-8.

## Background

Health inequities and community health are important areas of focus across the world. Public health policies should target health gaps to resolve current and future community health needs [1]. Interventions should focus on the social determinants of health which are the root causes of health inequities, to reduce vulnerabilities and address the unequal consequences of illness [2]. In particular, local governments must develop public health policies and effective inter-sectoral programs [3]. Additionally, public health nurses (PHNs) are responsible for improving a variety of health inequities, including the lack of limited access to healthcare services [4], as their unique professional roles provide a way to directly identify and address specific community health needs [5]. Local healthcare planning is a crucial strategy that PHNs can implement to reduce health inequities and bridge the gaps between community health needs [6]. In Japan, local healthcare plans include securing hospital beds, health and welfare services, and resources in each region to improve community health needs and equitable distribution of care [7].

PHNs may face challenges when developing competencies relevant to local healthcare planning [8, 9]. A systematic review demonstrated their necessary competencies, such as reflecting the narratives of community residents identified through providing individual care [9], determining the necessary programs and building consensus among those concerned [10, 11], and understanding policy and securing budget [12, 13]. To enhance these competencies and self-confidence among PHNs, continued education should be implemented [14, 15]. Web-based learning programs provide more advantages than traditional face-to-face group sessions and are often more flexible, user-friendly, convenient, and time-saving [16, 17]. However, there have been no randomized controlled trials (RCT) in this field [18, 19], and little is currently known about the effectiveness of web-based learning for PHNs [13, 17].

In Japan, approximately 60% of PHNs work for prefectural or municipal governments [20]. The national practice guidelines for PHNs published in 2013 increased their expected involvement in local healthcare planning [7]. Undergraduate curricula began to include these skills in 2007 [21], and the national PHN examination added related requirements in 2017 [22]. However, approximately 50% receive continued education relevant to local healthcare planning [23, 24]. Previous studies have not investigated whether PHNs who focused on self-directed learning improved self-confidence, competency, and readiness [25, 26].

Japan is facing a falling birth rate and an aging population. Consequently, local governments are promoting the reduction of public service positions despite the necessity of needs-oriented local healthcare plans [27]. The COVID-19 pandemic has also accelerated the growing shortage of PHNs [28], which emphasizes the need for effective and efficient educational programs targeted at improving competencies related to local healthcare planning. Thus, a web-based learning program would help PHNs understand theoretical concepts and practical strategies that are relevant to the healthcare planning process whenever they want without the need to contact other participants. Subsequently, this study will verify the effects/feasibility of a user-friendly web-based self-learning program designed to improve competencies for PHNs who are involved in the local healthcare planning process. Further, the study will verify the program outcomes and data collection methods using relevant scales and examine the preliminary effects of the web-based self-learning program, thus providing relevant data for calculating the sample size needed to conduct a future definitive RCT.

## Methods

### Trial design and settings

A pilot prospective RCT design will be implemented among single-blind participants and parallel groups. To ensure equal learning opportunities for both groups, PHNs who will answer a pre-test survey and register for this study will be randomly allocated to the intervention or wait-listed control groups [1:1]; as such, a double-blind design was not possible. All PHNs will be exposed to the same self-learning program; the intervention group will participate in the program first, and then, the wait-listed control group will be offered the same program. All participants will answer a post-test survey.

### Ethical considerations

The Institutional Review Board (IRB) at the organization affiliated with the primary researcher approved the protocol for this study on February 17, 2021 (ID: NIPH-IBRA#12313). The IRB of the third researcher also approved the study protocol on March 16, 2021 (ID: C1516).

This pilot study was registered with the University Hospital Medical Information Network Clinical Trials Registry (UMIN-CTR) following the International Committee of Medical Journal Editors (No. UMIN000043628, March 23, 2021). Explanations of the study’s aims and procedures will be provided to the participants through the study website. All eligible PHNs will provide written web-based informed consent prior to the study registration. Only those who will meet the inclusion criteria and agreed to participate will be included in the study. To ensure privacy, no personal information, including place of employment, will be collected.

### Participant eligibility criteria

Eligible participants will include PHNs who are full-time employees in Japan and have experience in local healthcare planning. Exclusion criteria will include those who do not have Internet access, are employed part-time, and have no opportunity to be involved in the local healthcare planning process.

### Sample size

The sample size has not yet been calculated using a power analysis due to feasibility and a limited research budget [29]. However, a rationale for numbers in the pilot trial should be included for pilot studies [30]. Based on our previous RCT, we estimate the participation rate would be approximately 2.4% [17]. In this pilot study, we will focus on a prefecture in the Kanto region in Japan, which has approximately 600 PHNs and 1,930,000 residents. Therefore, we will estimate that 14 PHNs were necessary for this study. Owing to ethical considerations, we do not over-recruit the participants. Further, we expect the participant pool to be limited due to the COVID-19 pandemic, which has resulted in a general shortage of PHNs because most will be involved in frontline activities [28].

### Sampling, informed consent, and randomization

The research team will send 36 invitations to participate (i.e., one to the prefectural government and 35 to the municipal governments) to public health nursing directors in May 2021 and a reminder letter in early June 2021. These directors will be asked to share information about this study with their PHNs. Those who will express interest in participation will be given access to our study website, which will contain a study explanation sheet and written web-based informed consent forms for completion. Only those who will agree to these conditions and will meet the eligibility criteria (as determined by the researchers) will be allowed to participate. The registration period will be from May until the end of June 2021. To ensure privacy, the participants will be registered using pseudonyms and their e-mail addresses.

Figure 1 illustrates a flowchart for the Consolidated Standards of Reporting Trial (CONSORT) design, which will be used throughout the study process. Randomization will be conducted by a researcher specializing in statistics and the co-author via an equal computer-based randomization table. A permuted-block method will be adopted to ensure that the participants will be equally divided between the intervention and control groups. In total, six blocks will be used with four sizes. We will send an e-mail to all participants informing them of their assigned group.

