### Description of the intervention: overview of the web-based self-learning program

We designed an outline of the web-based self-learning program, which included six modules for acquiring knowledge and skills related to local healthcare planning based on adult learning theory [31], a review of the relevant Japanese literature [13], and several specific studies [5, 7, 16, 17, 23, 24, 32]. In the pre-test, five PHNs with previous involvement in local healthcare planning will be asked to confirm the modules and content. We then added explanations for each module and confirmed that the newly developed web-based self-learning program will include knowledge and skills that PHNs could use to promote local healthcare planning effortlessly and effectively. Each module takes approximately 10–20 min to complete.

Table 1 presents the themes and objectives for each module as follows: (1) create a concrete vision of the ideal community, (2) bridge the daily practices of PHNs’ with local healthcare planning, (3) basic knowledge necessary for local healthcare planning, (4) understand the steps of the healthcare planning process, (5) hone coordinate skills with related parties, and (6) accomplish goal setting and project evaluation. The participants can use this worksheet to identify and summarize the objectives for local healthcare planning, community health needs, related government plans, legal issues, relevant staff and key persons in the community, and an evaluation index. The intervention will be conducted from July to August 2021. Once the post-test data will be collected in September 2021, the control group will participate in the program from October to November 2021.

**Table 1 Tab1:** Themes and objectives of each web-based self-learning module

	Module themes	Objectives
1	Create a concrete vision of the ideal community	Understand the viewpoints of creating a concrete vision of the ideal community
2	Bridge the daily practices of PHNs' with local healthcare planning	Envision the implementation of the Plan-Do-Check-Action cycle, from the evaluation of daily PHN practices to clarifying improvements and procedures Increase the motivation to bridge the daily practices of PHNs with the PDCA cycle
3	Basic knowledge necessary for local healthcare planning	Sort out the policies, programs, and projects involved in the plan you are helping to develop Understand the relationship between the plan involving PHNs and various other plans

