### Statistical analysis

We will conduct descriptive statistics (e.g., recruitment rate, dropout rate, and data completion rate) to assess the feasibility of this study and analyze intergroup baseline differences in the data and primary outcomes using the Mann-Whitney *U*-test and the chi-square/Fisher exact test. We will assess whether previous experience in local healthcare planning and other factors affected the study outcomes based on the results of the Mann-Whitney *U*-test and the chi-square/Fisher exact test. Analyses will be performed according to the intention-to-treat principle. We will use IBM SPSS for Windows (version 25; IBM Corp, Armonk, NY, USA) for the analysis and *p*-values < .05 indicating statistically significant intergroup differences. This study is expected to have a power ≥.80 and α ≤.05, assuming a medium effect size (*d* = .30) [35].

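### With 14 nurses, baseline primary scores known before allocation are used in neither the allocation nor the stated comparison, which costs precision in the preliminary effect estimate

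*Protocol article*

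**What the plan says.** All references are to the protocol article.

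- **Size.** Sample size gives a source population, "which has approximately 600 PHNs and 1,930,000 residents", and a rate, "we estimate the participation rate would be approximately 2.4" per cent, and concludes: "Therefore, we will estimate that 14 PHNs were necessary for this study".
- **Order of events.** Trial design and settings: "PHNs who will answer a pre-test survey and register for this study will be randomly allocated to the intervention or wait-listed control groups [1:1". Outcomes and data collection has the outcome scales completed at baseline, so the primary score precedes allocation.
- **Calendar.** Sampling, informed consent, and randomization closes registration at the end of June 2021. The description of the intervention says: "The intervention will be conducted from July to August 2021".
- **Allocation.** "A permuted-block method will be adopted to ensure that the participants will be equally divided between the intervention and control groups". The section mentions a computer-based table and six blocks. It names no stratification, matching or minimisation factor.
- **Analysis.** The team will "analyze intergroup baseline differences in the data and primary outcomes using the Mann-Whitney" U-test and chi-square or Fisher tests, at p < .05. No baseline-adjusted comparison is named.
- **Use of the result.** Background and Discussion want preliminary effects and data to size a definitive RCT. Discussion also says that the focus is feasibility, not effectiveness.

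**The concern.** The baseline value of an outcome is often the best available predictor of its post-test value. Here it is collected from everyone before allocation, and all nurses can be allocated together because registration ends before the modules open. The plan as described uses it only in a between-arm comparison at baseline, and such a test corrects nothing.

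With 7 nurses per arm, chance differences at baseline are large and part of each carries into the post-test comparison. At stake is the precision of the preliminary effect estimate that is meant to inform the definitive trial. The recruitment, dropout and completion rates do not depend on baseline balance.

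**Working it through.** **Inputs from the article.** About 600 nurses; 2.4% participation; 1:1 allocation; six blocks. No SD is given for the 16-item scale, so results are in SD units.

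**Assumptions.** Roughly normal scores with equal variance at both times; baseline to post-test correlation ρ = 0.5, 0.6 or 0.7 (not in the article); full follow-up unless stated.

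**1. The plan's own figure.** 600 × 0.024 = 14.4, so 14 reproduces, or 7 per arm.

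**2. Chance baseline difference.** SE = √(1/n1 + 1/n2) SD, and P(|difference| > 0.5 SD) = 2 × [1 − Φ(0.5/SE)].

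| Split | SE (SD) | P(> 0.5 SD) |
|---|---|---|
| 7 v 7 | 0.535 | 35.0% |
| 8 v 6 (blocks of four stopped at 14) | 0.540 | 35.5% |
| 12 v 12 (six blocks of four, all filled) | 0.408 | 22.1% |

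Simulation of 200,000 trials of 14 nurses gave 34.9% for a 7/7 split and 35.0% for truncated blocks of four.

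**3. What baseline adjustment gains with the allocation unchanged.** The unadjusted mean difference has variance 2/7 = 0.286 (SD 0.535). With one baseline covariate the expected variance is (1 − ρ²) × (2/7) × [1 + 1/(N − 4)], where N is the number analysed. At N = 14 the last factor is 1.1. Simulation gives the same SDs.

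| ρ | SD unadjusted | SD adjusted | Variance cut |
|---|---|---|---|
| 0.5 | 0.535 | 0.485 | 1 − (0.485/0.535)² = 18% |
| 0.6 | 0.535 | 0.447 | 1 − (0.447/0.535)² = 30% |
| 0.7 | 0.535 | 0.400 | 1 − (0.400/0.535)² = 44% |

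**4. What pairing on the baseline rank adds to adjustment.** The SDs fall to 0.465, 0.427 and 0.385. The further variance cuts are 1 − (0.465/0.485)² = 8.1%, 1 − (0.427/0.447)² = 8.7% and 1 − (0.385/0.400)² = 7.4%, so about 8%.

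**5. Balance under pairing, with random dropout.** P(baseline gap > 0.5 SD) among completers, by simulation, requiring at least two completers per arm:

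| Loss | Paired | Unpaired |
|---|---|---|
| 0% | 0.3% | 35% |
| 20% | 14% | 41% |
| 50% | 39% | 51% |

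**6. Adjustment when few complete.** Assessment of the trial feasibility sets data completion at 50%, which is 7 of 14 nurses. The small-sample factor in step 3 becomes 1 + 1/3 = 1.33. The variance ratio (1 − ρ²) × 1.33 is then 1.00, 0.85 and 0.68, so the cuts shrink to about 0%, 15% and 32%.

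**7. Interval width at ρ = 0.6, full follow-up.** 1.96 × SD gives 1.05 SD unadjusted, 0.88 SD adjusted, and 0.84 SD adjusted and paired.

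**The case against.** Unstratified permuted blocks are a standard and valid method, and the article claims only that they equalise numbers. Chance imbalance is already part of the sampling error of a randomised comparison. Discussion puts feasibility ahead of effectiveness, and no feasibility criterion uses the effect estimate. All of this stands, and it limits the point to precision.

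Three stronger readings are tempting, and the article does not support them.

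- **A post-test difference could not be attributed to the program.** Randomisation stays valid, and a proper interval already allows for chance imbalance.
- **The allocation method is the fault, and pairing cures it.** Step 3 shows that most of the gain comes from adjustment with the allocation left alone. The 0.3% under pairing needs complete follow-up. At 50% loss it is about 39%.
- **Carry-over larger than the article's d = .30 in 35% of trials is a second problem.** At ρ = 0.6 it is the same event as a 0.5 SD baseline gap, since 0.6 × 0.5 = 0.30. It is 26% at ρ = 0.5 and 42% at ρ = 0.7.

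It can also be said that adjustment belongs in a fuller analysis plan. But the article states its comparison, and that comparison omits baseline. Nor does it say whether post-test or change scores are compared. If change scores are meant, their SD is √[2(1 − ρ) × 2/7] = 0.535, 0.478 and 0.414, and adjustment gains less: 18%, 13% and 7%.

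Finally, even the best option leaves a half-width of about 0.84 SD. That is a consequence of N = 14, which neither change removes.

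**Conclusion.** The point holds as a matter of efficiency. The article collects the baseline primary score before allocation and uses it in neither the allocation nor the stated comparison of arms. At 7 v 7 a chance baseline gap above 0.5 SD occurs in about 35% of trials, or 22% if 24 nurses are enrolled.

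Against an unadjusted post-test comparison, a covariate cuts the variance of the mean difference by about 18% to 44% over ρ = 0.5 to 0.7. Pairing adds about 8%. These figures rest on approximate normality, the assumed correlations and full follow-up. They describe a difference in means, not the Mann-Whitney test itself. The gain is smaller if change scores are meant or if few nurses complete.

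There is no bias and no threat to the feasibility assessment. The change is worth making because the data are already collected.

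**What to change.** **Main change, in Statistical analysis.** Estimate the between-arm difference in the post-test 16-item score with the baseline score as covariate, and report it with a confidence interval. Describe the arms at baseline and drop the significance tests of baseline differences. This needs no new data. The cost is one covariate, which is unstable if very few nurses complete (7 completers leave 7 − 3 = 4 residual degrees of freedom), so the unadjusted difference should be shown beside it.

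**Optional addition, in Sampling, informed consent, and randomization.** Allocate once, after registration closes. Rank the registered nurses by baseline score and randomise within adjacent pairs, allocating an unpaired last nurse at random. Keep the score as the covariate, so that a lost partner does not remove the other nurse from the analysis. The cost is that allocation waits until the end of June, which still precedes the July start. The benefit is small and falls with dropout.

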**Fig. 1 Fig1:**
[figure not shown]
Consolidated Standards of Reporting Trial (CONSORT) flowchart

### Minimizing bias

All data will be anonymized, and we will not collect any personal information or the names of the local governments where the participants are employed. The data collection will be conducted through the study website, where the participants will enter the relevant information and will complete the required elements (e.g., demographic data and the outcome scales); this information will be evaluated as baseline and post-test data. The intervention group will be asked to keep the contents of the web-based self-learning program confidential so that the control group will not be exposed to any such information. The risks of contaminating the intervention group will be explained on the study website, and the intervention group will receive a URL password-protected (passwords sent via e-mail) address to view the learning modules.

### Description of the intervention: overview of the web-based self-learning program

We designed an outline of the web-based self-learning program, which included six modules for acquiring knowledge and skills related to local healthcare planning based on adult learning theory [31], a review of the relevant Japanese literature [13], and several specific studies [5, 7, 16, 17, 23, 24, 32]. In the pre-test, five PHNs with previous involvement in local healthcare planning will be asked to confirm the modules and content. We then added explanations for each module and confirmed that the newly developed web-based self-learning program will include knowledge and skills that PHNs could use to promote local healthcare planning effortlessly and effectively. Each module takes approximately 10–20 min to complete.

Table 1 presents the themes and objectives for each module as follows: (1) create a concrete vision of the ideal community, (2) bridge the daily practices of PHNs’ with local healthcare planning, (3) basic knowledge necessary for local healthcare planning, (4) understand the steps of the healthcare planning process, (5) hone coordinate skills with related parties, and (6) accomplish goal setting and project evaluation. The participants can use this worksheet to identify and summarize the objectives for local healthcare planning, community health needs, related government plans, legal issues, relevant staff and key persons in the community, and an evaluation index. The intervention will be conducted from July to August 2021. Once the post-test data will be collected in September 2021, the control group will participate in the program from October to November 2021.

**Table 1 Tab1:** Themes and objectives of each web-based self-learning module

	Module themes	Objectives
1	Create a concrete vision of the ideal community	Understand the viewpoints of creating a concrete vision of the ideal community
2	Bridge the daily practices of PHNs' with local healthcare planning	Envision the implementation of the Plan-Do-Check-Action cycle, from the evaluation of daily PHN practices to clarifying improvements and procedures Increase the motivation to bridge the daily practices of PHNs with the PDCA cycle
3	Basic knowledge necessary for local healthcare planning	Sort out the policies, programs, and projects involved in the plan you are helping to develop Understand the relationship between the plan involving PHNs and various other plans
4	Understand the steps of the healthcare planning process	Understand the overall schedule and development process of planning Understand the nature of goal setting for each program and project
5	Hone coordination skills with related parties	Understand how to set up the committees/meetings necessary for planning Understand how to collaborate with related persons and residents in order to utilize the plan in daily PHN practices
6	Accomplish goal setting and project evaluation	Understand the list of target values related to national/prefectural governments Establish project objectives that are consistent with the target values of national/prefectural governments

